**5.3.16. Visit 12 (60 months  $\pm$ 30 days)**

- Review of continuing ability to consent/Advance Directive
- Review willingness to share contact information with FOUND or, if enrolled in FOUND, review individual status report
- PPMI Brain and Tissue Bank (for subjects who did not yet sign a form providing permission to be contacted by the Brain and Tissue Bank study team or have not yet signed an Intent to Donate form, review subject interest in PPMI Brain and Tissue Bank and remind interested subjects to follow up with the Brain and Tissue Bank study team or have subject sign an Intent to Donate form)
- General neurological examination
- Height and weight
- Vital signs (blood pressure, heart rate and temperature)
- Clinical laboratory assessments
- Blood draw for research samples
- Urine collection for research samples
- PASE Exercise Questionnaire
- Epworth Sleepiness Scale
- REM Sleep Behavior Disorder Questionnaire
- GDS-15
- State-Trait Anxiety Inventory
- Questionnaire for Impulsive-Compulsive Disorders
- SCOPA-AUT

- Montreal Cognitive Assessment (MoCA)
- Letter Number Sequencing
- Hopkins Verbal Learning Test – Revised (Form 6)
- Symbol Digit Modalities Test (Form 2)
- Benton Judgment of Line Orientation (Even items)
- Semantic Fluency
- Cognitive Categorization Assessment
- MDS-UPDRS Parts I-III (Part IV also conducted at each visit for subjects who have started PD medication)
- Hoehn and Yahr
- Modified Schwab & England (PD, prodromal, PD and Unaffected Genetic Cohort subjects only)
- MDS-UPDRS Part III and Hoehn & Yahr will be repeated one hour following dosing in clinic for subjects who have started levodopa or dopamine agonist
- Review of clinical diagnosis
- Review of family history of PD (Genetic Cohort subjects only)
- Lumbar puncture for collection of CSF
- MRI DTI and resting state (PD and Genetic Cohort subjects at selected sites; HC at selected sites if resting state sequences were not obtained at a previous visit).
- [F] florbetaben PET imaging at selected sites, PD (idiopathic and genetic cohorts), HC and Prodromal (genetic cohort) subjects if not done at V04 or V06 or V10; (or may be done at V13 (month 72), V14 (month 84) or V15 (month 96) for PD and HC cohorts); see companion protocol.
- Gait assessments, at selected sites (Genetic Cohort subjects only) (see section 6.3.9 for details)
- Review of current medical conditions
- Review of concomitant medications
- Review of adverse events related to lumbar puncture
- Consent/withdrawal of consent for contact regarding future studies related or unrelated to PPMI

After January 1 2019, all subjects completing visits post month 60/visit 12 will follow a modified schedule of activities. This applies to all cohorts. Please see the section below titled “Modified Schedule of Activities” for details on the assessments and procedures to be completed at post V12 visits after January 1, 2019.

**5.3.17. Visit 13 (72 months  $\pm$ 30 days)- (Parkinson Disease and Healthy Control Subjects only prior to January 1, 2019)**

- Review of continuing ability to consent/Advance Directive
- Review willingness to share contact information with FOUND or, if enrolled in FOUND, review individual status report
- PPMI Brain and Tissue Bank (for subjects who did not yet sign a form providing permission to be contacted by the Brain and Tissue Bank study team or have not yet signed an Intent to Donate form, review subject interest in PPMI Brain and Tissue Bank and remind interested subjects to follow up with the

Brain and Tissue Bank study team or have subject sign an Intent to Donate form)

- General neurological examination
- Height and weight
- Vital signs (blood pressure, heart rate and temperature)
- Clinical laboratory assessments
- Blood draw for research samples
- Urine collection for research samples
- PASE Exercise Questionnaire
- Epworth Sleepiness Scale
- REM Sleep Behavior Disorder Questionnaire
- GDS-15
- State-Trait Anxiety Inventory
- Questionnaire for Impulsive-Compulsive Disorders
- SCOPA-AUT
- Montreal Cognitive Assessment (MoCA)
- Letter Number Sequencing
- Hopkins Verbal Learning Test – Revised (Form 1)
- Symbol Digit Modalities Test (Form 1 )
- Benton Judgment of Line Orientation (odd items)
- Semantic Fluency
- Cognitive Categorization Assessment
- MDS-UPDRS Parts I-III (Part IV also conducted at each visit for subjects who have started PD medication)
- Hoehn and Yahr
- Modified Schwab & England (PD only)
- MDS-UPDRS Part III and Hoehn & Yahr will be repeated one hour following dosing in clinic for subjects who have started levodopa or dopamine agonist
- Review of clinical diagnosis
- Lumbar puncture for collection of CSF (optional)
- [F] florbetaben PET imaging at selected sites, PD (idiopathic cohort) subjects if not done at V04, V06, V10 or V12; (or may be done at V14 (month 84) or V15 (month 96) for PD and HC cohorts); see companion protocol.
- Review of current medical conditions
- Review of concomitant medications
- Review of adverse events related to lumbar puncture (if lumbar puncture performed)
- Consent/withdrawal of consent for contact regarding future studies related or unrelated to PPMI

**5.3.18. Visit 14 (84 months  $\pm$ 30 days) (Parkinson Disease and Healthy Control Subjects only prior to January 1, 2019)**

- Review of continuing ability to consent/Advance Directive
- Review willingness to share contact information with FOUND or, if enrolled in FOUND, review individual status report
- PPMI Brain and Tissue Bank (for subjects who did not yet sign a form providing permission to be contacted by the Brain and Tissue Bank study team or have not yet signed an Intent to Donate form, review subject interest in PPMI Brain and Tissue Bank and remind interested subjects to follow up with the Brain and Tissue Bank study team or have subject sign an Intent to Donate form)
- General neurological examination
- Height and weight
- Vital signs (blood pressure, heart rate and temperature)
- Clinical laboratory assessments
- Blood draw for research samples
- Urine collection for research samples
- PASE Exercise Questionnaire
- Epworth Sleepiness Scale
- REM Sleep Behavior Disorder Questionnaire
- GDS-15
- State-Trait Anxiety Inventory
- Questionnaire for Impulsive-Compulsive Disorders
- SCOPA-AUT
- Montreal Cognitive Assessment (MoCA)
- Letter Number Sequencing
- Hopkins Verbal Learning Test – Revised (Form 2)
- Symbol Digit Modalities Test (Form 2 )
- Benton Judgment of Line Orientation (even items)
- Semantic Fluency
- Cognitive Categorization Assessment
- MDS-UPDRS Parts I-III (Part IV also conducted at each visit for subjects who have started PD medication)
- Hoehn and Yahr
- Modified Schwab & England (PD only)
- MDS-UPDRS Part III and Hoehn & Yahr will be repeated one hour following dosing in clinic for subjects who have started levodopa or dopamine agonist
- Review of clinical diagnosis
- Lumbar puncture for collection of CSF (optional)
- [ $^{18}\text{F}$ ] florbetaben PET imaging at selected sites, PD (idiopathic cohort) or HC subjects if not done at V04, V06, V10, V12 or V13; (or may be done V15 (month 96) for PD cohort); see companion protocol.
- Review of current medical conditions
- Review of concomitant medications

- Review of adverse events related to lumbar puncture (if lumbar puncture performed)
- Consent/withdrawal of consent for contact regarding future studies related or unrelated to PPMI

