† Intent to Donate documentation completed with PPMI Brain and Tissue Bank study team or local PPMI site based on accessibility, local regulations and availability of infrastructure. For subjects who have not yet been approached concerning the Brain and Tissue Bank, please review subject interest in providing permission to forward their contact information to the PPMI Brain and Tissue Bank study team at their next visit (including interim visits). For subjects who may have already been approached concerning the Brain and Tissue Bank, but were undecided concerning participation or who have not yet signed an Intent to Donate form- please review Brain and Tissue Bank with subject at next annual visit (sites may also review this at interim visits if site deems appropriate).

o Urine (or serum) pregnancy test prior to injection for women of childbearing potential.

p Serum pregnancy test prior to injection day for women of childbearing potential; ECG for all subjects.

r Subjects enrolled in U.S. may agree to initial VMAT imaging scan at YR01 rather than Screening.s [18F]

s florbetaben PET imaging at selected sites (see companion protocol) at either Month 24, 36, 48, 60, 72, 84 or 96t Skin biopsy for participating sites completed at any routine or unscheduled visit post amendment approval; for sites collecting blood samples as part of companion study, blood draw completed at unscheduled visit post amendment approval.

t Skin biopsy for participating sites completed at any routine or unscheduled visit post amendment approval; for sites collecting blood samples as part of companion study, blood draw completed at unscheduled visit or interim visit post amendment approval. (sites completing collection of blood sample at interim visit must forego collection of PBMCs and biomic blood samples at interim visit)

ST = Symptomatic Therapy

PW = Premature Withdrawal (\*if not done in last 3 mths; ^if not done in last 12 mths; +if subject has not completed scan and is willing to complete at PW )

# For active subjects, begin at next visit post amendment approval and consent

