j Repeat assessment 1hr post treatment for subjects on levodopa or dopamine agonist.

k Not conducted depending on when ST visit completed – see protocol Sect. 5.3.20.

m DAT completed at all sites except Australia; VMAT completed in Australia and selected U.S. sites.

o Urine (or serum) pregnancy test prior to injection for women of childbearing potential.

p Serum pregnancy test prior to injection day for women of childbearing potential.

r Subjects enrolled in U.S. may agree to initial VMAT imaging scan at YR01 rather than Screening.

s [F] florbetaben PET imaging at selected sites (see companion protocol) at either Month 24, 36, 48, or 60 (what about month 84?)

t Skin biopsy for participating sites completed at any routine or unscheduled visit post amendment approval; for sites collecting blood samples as part of companion study, blood draw completed at unscheduled visit or interim visit post amendment approval. (sites completing collection of blood sample at interim visit must forego collection of PBMCs and biomic blood samples at interim visit)  
PV= Phone Visit

PW = Premature Withdrawal (\*if not done in last 3 mths; ^ only if withdrawal within first 12 mths and MRI DTI not done in last 6 mths)

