**5.3.12. Visit 08 (36 months  $\pm$ 30 days)**

- Review of continuing ability to consent/Advance Directive
- Review willingness to share contact information with FOUND or, if enrolled in FOUND, review individual status report
- PPMI Brain and Tissue Bank (for subjects who did not yet sign a form providing permission to be contacted by the Brain and Tissue Bank study team or have not yet signed an Intent to Donate form, review subject interest in PPMI Brain and Tissue Bank and remind interested subjects to follow up with the Brain and Tissue Bank study team or have subject sign an Intent to Donate form)
- General neurological examination

- Height and weight
- Vital signs (blood pressure, heart rate and temperature)
- Clinical laboratory assessments
- Blood draw for research samples
- Urine collection for research samples
- PASE Exercise Questionnaire
- Epworth Sleepiness Scale
- REM Sleep Behavior Disorder Questionnaire
- GDS-15
- State-Trait Anxiety Inventory
- Questionnaire for Impulsive-Compulsive Disorders
- SCOPA-AUT
- Montreal Cognitive Assessment (MoCA)
- Letter Number Sequencing
- Hopkins Verbal Learning Test – Revised (Form 4)
- Symbol Digit Modalities Test (Form 2)
- Benton Judgment of Line Orientation (Even items)
- Semantic Fluency
- Cognitive Categorization Assessment
- UPSIT (Prodromal and Unaffected Genetic Cohort subjects only; if subject has already completed their month 36 visit at time of amendment 12 approval, this may be completed at a later visit)
- MDS-UPDRS Parts I-III (Part IV also conducted at each visit for subjects who have started PD medication)
- Hoehn and Yahr
- Modified Schwab & England (PD, Prodromal, and Genetic Cohort subjects only)
- MDS-UPDRS Part III and Hoehn & Yahr will be repeated one hour following dosing in clinic for subjects who have started levodopa or dopamine agonist
- SPECT imaging (Prodromal subjects only), includes urine (or serum if required by site) pregnancy test for women of childbearing potential prior to injection
- [F] florbetaben PET imaging at selected sites, PD (idiopathic and genetic cohorts), HC, and Prodromal (including RBD, olfactory and genetic cohort) subjects if not done at V04 or V06; or may be done at V10 (48 months) or V12 (60 months); (or at V13 (month 72), V4 (month 84) or V15 (month 96) for PD and HC cohorts); see companion protocol.
- MRI-DTI and resting state, HC at selected sites if not obtained at a previous visit

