- [F] florbetaben PET imaging at selected sites, PD (idiopathic and genetic cohorts), HC, and Prodromal (including RBD, olfactory and genetic cohort) subjects if not done at V04, V06 or V08; or may be done at V12 (60 months); (or at V13 (month 72), V14 (month 84) or V15 (month 96) for PD and HC cohorts); see companion protocol.
- Gait assessments, at selected sites (Genetic Cohort subjects only) (see section 6.3.9 for details)
- Review of current medical conditions
- Review of concomitant medications
- Review of adverse events in follow up to SPECT imaging (and/or VMAT-2 PET) and/or lumbar puncture
- Consent/withdrawal of consent for contact regarding future studies related or unrelated to PPMI

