#### **6.3.3. [ $^{18}\text{F}$ ] florbetaben PET imaging**

[Refer to the *Evaluation of [ $^{18}\text{F}$ ] florbetaben in Subjects Participating in the Parkinson's Progression Markers Initiative* companion protocol]

Subjects participating at selected PPMI sites will undergo [ $^{18}\text{F}$ ] florbetaben PET imaging at either their Month 12, 24, 36, 48, 60, 72, 84 or 96 visit to evaluate an investigational imaging agent [ $^{18}\text{F}$ ] florbetaben, as a tracer for the visual detection of beta-amyloid in the brain.

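### The florbetaben scan checks from Month 60 on leave out Month 36, so a subject scanned then meets the written condition for a second tracer injection; separately, the PD and HC scan windows conflict

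*Protocol*

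**What the plan says.** Florbetaben PET is done at selected sites in about 200 subjects (Protocol 4.1.1.2). Section 6.3.3 calls the agent investigational and places the scan "at either their Month 12, 24, 36, 48, 60, 72, 84 or 96 visit", which describes one visit out of a set. The schedule footnotes use the same construction. At premature withdrawal (5.3.23) the scan is offered only to a subject who has not already had it.

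Each annual visit has its own check on earlier scans:

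- V08, Month 36 (5.3.12): "subjects if not done at V04 or V06; or may be done at V10 (48 months) or V12 (60 months".
- V10, Month 48 (5.3.14): "subjects if not done at V04, V06 or V08; or may be done at V12 (60 months".
- V12, Month 60 (5.3.16): PD (idiopathic and genetic cohorts), "HC and Prodromal (genetic cohort) subjects if not done at V04 or V06 or V10".
- V13, Month 72 (5.3.17): "PD (idiopathic cohort) subjects if not done at V04, V06, V10 or V12".
- V14, Month 84 (5.3.18): "PD (idiopathic cohort) or HC subjects if not done at V04, V06, V10, V12 or V13".
- V15, Month 96 (5.3.19): idiopathic PD only, checking V04, V06, V10, V12, V13 and V14.

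On the windows, footnote s of the PD schedule reads "florbetaben PET imaging at selected sites (see companion protocol) at either Month 24, 36, 48, 60, 72, 84 or 96". Footnote s of the HC schedule reads "at either Month 24, 36, 48, or 60 (what about month 84", ending in a question mark that nobody has answered.

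**The concern.** The check at each visit is the rule a coordinator applies on the day. Month 36 is a permitted scan visit, yet it drops out of every check from Month 60 on, so a subject already scanned can pass as unscanned. What is at stake is an injection of an investigational radiotracer that the single-scan wording elsewhere in the protocol does not provide for.

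The conflicting windows are a second, independent defect. Sites cannot tell from this document when idiopathic PD scanning begins or when HC scanning ends, and an open drafting question sits in an operative schedule.

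**Working it through.** No sample-size or power figure is involved, so the check is a comparison of passages.

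**Step 1. Trace a subject scanned only at V08 (Month 36).**

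| Visit | Cohorts named | Earlier visits checked | Condition met? |
|---|---|---|---|
| V10, Month 48 (5.3.14) | PD, HC, all prodromal | V04, V06, V08 | No |
| V12, Month 60 (5.3.16) | PD, HC, genetic-cohort prodromal | V04, V06, V10 | **Yes** |
| V13, Month 72 (5.3.17) | idiopathic PD | V04, V06, V10, V12 | **Yes** |
| V14, Month 84 (5.3.18) | idiopathic PD, HC | V04, V06, V10, V12, V13 | **Yes** |
| V15, Month 96 (5.3.19) | idiopathic PD | V04, V06, V10, V12, V13, V14 | **Yes** |
| Premature withdrawal (5.3.23) | any not yet scanned | all earlier visits | No |

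The checks at V06, V08 and V10 cover every earlier scan visit. The four at V12 to V15 each miss exactly one, and always V08. A scan at V12 or later is counted by every list after it, so the literal wording admits at most one repeat per subject.

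**Step 2. Limits on the route.** V12 names prodromal subjects of the genetic cohort only. RBD and hyposmia subjects may be scanned at Month 36 under 5.3.12 but are not named at V12, and their own footnote stops at Month 48. The headings of 5.3.17 to 5.3.19 confine V13 to V15 to PD and HC subjects before January 1, 2019; the modified schedule that follows has no florbetaben entry. The V12 route is not affected by that date.

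**Step 3. Idiopathic PD, start of window.** Section 5.3.8 names the idiopathic cohort at Month 12. The PD schedule row has its first mark at V06 (Month 24), and the PD footnote also starts at Month 24. The difference is 24 − 12 = 12 months.

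**Step 4. HC, end of window.**

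| Place | HC scan visits |
|---|---|
| HC footnote s | Months 24 to 60, with the open query about Month 84 |
| HC schedule row | marks to Month 60, then one at V14 (Month 84); none at V13 or V15 |
| Forward-pointing text in the annual visits from 5.3.8 to 5.3.16 | adds Months 72, 84 and 96 for PD and HC |
| 5.3.17 (Month 72) | scan entry names idiopathic PD only, but points HC on to Month 84 or 96 |
| 5.3.18 (Month 84) | names HC; Month 96 kept for PD |
| 5.3.19 (Month 96) | names idiopathic PD only |

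The HC end is therefore Month 60, 84 or 96, a spread of 96 − 60 = 36 months.

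**The case against.** The best reply is that nobody intends a second scan. The wording of 6.3.3 and the footnotes points to one visit, and the withdrawal rule looks back over all earlier visits. A repeat needs one visit list read on its own. In addition, 5.2 sends participating sites to the companion protocol for the florbetaben schedule, and that document, not shown here, may limit the number of scans. Both points stand: this is very probably a drafting omission. They do not remove the defect, because the visit text still gives a different answer from the rest of the protocol.

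The date limit on V13 to V15 also stands and leaves V12 as the main route. The titles of the PD and HC schedules put the changeover at the later of January 1, 2019 and V15; I follow the visit headings and the text after 5.3.16, which give the narrower route.

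A reader might infer more than the documents support:

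- *Every subject scanned at Month 36 qualifies again.* No: RBD and hyposmia prodromal subjects are not named at V12.
- *Section 6.3.3 puts idiopathic PD at Month 12.* It pools all cohorts, and the prodromal and genetic-cohort footnotes do start at Month 12. The conflict for idiopathic PD rests on 5.3.8 alone.
- *The unclear windows bias a PD-versus-HC amyloid comparison.* Section 14 states no such comparison, and 6.3.3 gives the purpose as evaluating the tracer.
- *The window conflict causes the repeat injection.* It does not; that follows only from the missing V08.

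**Conclusion.** The point holds as an internal contradiction. Four of the four visit checks from Month 60 on omit V08. Read literally, each admits one repeat injection for the cohorts it names, against the single-scan wording and the withdrawal rule. The number of subjects exposed cannot be computed: the protocol does not say how many were scanned at Month 36, and about 200 is the whole companion sample, hence a ceiling and not an estimate. The conclusion assumes that sites apply the visit text as written and that the companion protocol does not already prevent a repeat.

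The window conflicts are separate and also real: 12 months at the start for idiopathic PD, and up to 36 months at the end for HC. The documents do not settle which window is right, and I do not choose one. Nothing here touches the analyses described in Section 14. The text should be corrected because it bears on radiotracer exposure and costs little to put right.

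**What to change.** 1. Reconcile the checks on earlier scans in 5.3.16 to 5.3.19 with 5.3.12, 5.3.14, 6.3.3 and the withdrawal rule in 5.3.23, so that all give the same answer for a subject scanned at Month 36.
2. Reconcile the start of the idiopathic PD window and the end of the HC window across the schedule rows, the footnotes, the visit text and the companion protocol.
3. Resolve the query in HC footnote s and delete it.

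The cost is a text correction in the next amendment and a short notice to the imaging sites.

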**5.3.19 Visit 15 (96 months  $\pm$ 30 days) (Parkinson Disease and Healthy Control Subjects prior to January 1, 2019)**

- Review of continuing ability to consent/Advance Directive
- Review willingness to share contact information with FOUND or, if enrolled in FOUND, review individual status report
- PPMI Brain and Tissue Bank (for subjects who did not yet sign a form providing permission to be contacted by the Brain and Tissue Bank study team or have not yet signed an Intent to Donate form, review subject interest in PPMI Brain and Tissue Bank and remind interested subjects to follow up with the Brain and Tissue Bank study team or have subject sign an Intent to Donate form) General neurological examination
- Height and weight
- Vital signs (blood pressure, heart rate and temperature)
- Clinical laboratory assessments
- Blood draw for research samples
- Urine collection for research samples
- PASE Exercise Questionnaire
- Epworth Sleepiness Scale
- REM Sleep Behavior Disorder Questionnaire
- GDS-15
- State-Trait Anxiety Inventory
- Questionnaire for Impulsive-Compulsive Disorders
- SCOPA-AUT
- Montreal Cognitive Assessment (MoCA)
- Letter Number Sequencing
- Hopkins Verbal Learning Test – Revised (Form 3)
- Symbol Digit Modalities Test (Form 1)
- Benton Judgment of Line Orientation (odd items)
- Semantic Fluency
- Cognitive Categorization Assessment
- MDS-UPDRS Parts I-III (Part IV also conducted at each visit for subjects who have started PD medication)
- Hoehn and Yahr
- Modified Schwab & England (PD only)
- MDS-UPDRS Part III and Hoehn & Yahr will be repeated one hour following dosing in clinic for subjects who have started levodopa or dopamine agonist
- Review of clinical diagnosis
- Lumbar puncture for collection of CSF (optional)

- [F] florbetaben PET imaging at selected sites, PD (idiopathic cohort) subjects if not done at V04, V06, V10, V12, V13 or V14; see companion protocol.
- Review of current medical conditions
- Review of concomitant medications
- Review of adverse events related to lumbar puncture (if lumbar puncture performed)
- Consent/withdrawal of consent for contact regarding future studies related or unrelated to PPMI

